##### Missing Data

Every effort was made to minimize missing primary outcome data. However, the primary analytic strategy relies on mixed effects models, which is unbiased under missing-at-random assumptions and is the most frequently accepted approach in longitudinal data analysis [87]. Characteristics of patients who are lost to follow-up will be compared to those who complete the study to assess the degree of any selection bias due to attrition. We will complete a sensitivity analysis to compute indices of sensitivity to the nonignorability of missing data. If these analyses indicate evidence that nonignorability will impact model parameter estimation, we will apply fully conditional specification multiple imputation methods, which are applicable to nonignorable missing data [87,88].

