#### Preliminary Effectiveness

##### Analytic Sample

The primary analytic sample will include all participants who completed the baseline survey; this will serve as the intention-to-treat sample. We will also conduct modified intention-to-treat analyses including only participants who attended 1 THRIVE session.

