## Results

Recruitment, enrollment, and data collection from the 3 sites was completed between June 2024 and March 2025. Of the 92 women recruited and enrolled, 71 (77%) completed the intervention and postintervention assessments, 58 (63%) completed the 1-month follow-up assessments, and 44 (48%) completed the 3-month follow-up assessments. Ten completers, 2 noncompleters, and 2 PSS completed exit interviews. Of the 92 enrolled participants, 45 (50%) were from the Prisma Health Addiction Medicine Center, 42 (47%) from Phoenix Center, and 3 (3%) from Magdalene Clinic. Of the 92 participants, 1 (1%) was American Indian or Alaska Native, 4 (4%) were Black, 1 (1%) were Hispanic, 79 (86%) were White, 2 (2%) identified as multiracial, and 3 (3%) identified as “other.” Racial and ethnic distribution is representative of the patient populations at the recruitment sites. The participants’ mean age was 35 (SD 9.87) years. The most commonly reported substances used included tobacco (79/92, 86%), cannabis (58/92, 63%), alcohol (55/92, 61%), amphetamine-type stimulants (58/92, 63%), and opioids (50/92, 54%; Table 3).

**Table 3 table3:** Types of substances used by enrolled participants (N=92).

Substance types	Participants, n (%)
Tobacco	79 (86)
Alcohol	55 (61)
Cannabis	58 (63)
Opioids (heroin, fentanyl, etc)	50 (54)
Amphetamine-type stimulants	58 (63)
Inhalants	19 (24)
Sedatives	47 (51)
Hallucinogens	32 (35)
Cocaine	44 (48)

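### The planned remedy for nonignorable dropout is fully conditional specification imputation with no nonignorable component stated, so as written it returns to missing at random

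*Protocol article*

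**What the plan says.** The Analytic Sample section defines the main analysis set: "The primary analytic sample will include all participants who completed the baseline survey; this will serve as the intention-to-treat sample".

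The Missing Data section then sets out the handling of dropout:

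- **Primary analysis:** "the primary analytic strategy relies on mixed effects models, which is unbiased under missing-at-random assumptions".
- **Attrition check:** women lost to follow-up are compared with completers on their characteristics.
- **Sensitivity analysis:** "We will complete a sensitivity analysis to compute indices of sensitivity to the nonignorability of missing data".
- **Conditional remedy:** the condition is "If these analyses indicate evidence that nonignorability will impact model parameter estimation", and the action is "we will apply fully conditional specification multiple imputation methods, which are applicable to nonignorable missing data".

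No shift parameter, pattern-mixture term, selection model or other departure from MAR is attached to the imputation.

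The Results section gives the follow-up achieved. Out of 92 enrolled women, 71 were assessed after the intervention and 58 at 1 month. For the last time point it reports that "44 (48%) completed the 3-month follow-up assessments".

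**The concern.** FCS is a way of building an imputation model one variable at a time. In its standard form each conditional model is fitted to women whose value was observed, and missing values are drawn from that model. This treats the missing values as exchangeable with observed ones given the predictors, which is the MAR assumption already made by the mixed models. FCS becomes a nonignorable method only when something is added that makes the missing differ from the observed, and the article adds nothing.

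The remedy is used only when the indices suggest that MAR is not good enough. An MAR method at that point cannot correct the problem that triggered it. Yet the sentence tells the analyst that it does, and an analysis plan that follows the sentence takes over the error.

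Outcome-related dropout is plausible on the article's own account. The Introduction links a history of violence to relapse and poor recovery, and the Discussion says that exposure to violence can lead to escalating substance use. The 1- and 3-month surveys were completed remotely from links sent by text or email. With one arm, there is no comparator in which similar dropout could partly offset the bias.

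**Working it through.** **1. Missing fractions.** Inputs are from the Results: 92 enrolled; 71, 58 and 44 assessed.

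| Time point | Assessed | Missing | Missing fraction f |
|---|---|---|---|
| After the intervention | 71/92 = 77.2% | 21 | 0.228 |
| 1 month | 58/92 = 63.0% | 34 | 0.370 |
| 3 months | 44/92 = 47.8% | 48 | 0.522 |

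The article's 77%, 63% and 48% are reproduced. This takes all 92 as baseline respondents. The site counts in the Results add to 45 + 42 + 3 = 90; on a denominator of 90 the missing fractions would be 19/90 = 21%, 32/90 = 36% and 46/90 = 51%, which changes nothing below.

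**2. Effect of a departure from MAR.** Let the mean among missing women be their MAR prediction plus delta.

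- True mean = (1 − f) × observed mean + f × (MAR prediction + delta)
- MAR estimate = (1 − f) × observed mean + f × MAR prediction
- Difference = f × delta

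The factor f comes from the article. Delta does not, so it is an assumption. At 3 months an assumed range of 0.2 to 1.0 SD gives 0.522 × 0.2 = 0.10 SD to 0.522 × 1.0 = 0.52 SD. For an assumed 0.5 SD:

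- after the intervention: 0.228 × 0.5 = 0.11 SD
- 1 month: 0.370 × 0.5 = 0.18 SD
- 3 months: 0.522 × 0.5 = 0.26 SD

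Standard FCS sets delta to 0, so it recovers none of these amounts.

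**3. Illustrative simulation of FCS against likelihood under MAR.** All inputs are assumptions: baseline and 3-month scores bivariate normal, SD 1, correlation 0.6, true change −0.30 SD, about 52% missing at 3 months. Missingness is logistic with slope 1 per SD, on the baseline score (MAR) or on the unseen 3-month score (nonignorable). Imputation is standard normal regression.

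| Missingness | True change | Standard FCS | Maximum likelihood under MAR |
|---|---|---|---|
| MAR (n = 92, 1,000 runs) | −0.30 | −0.30 | −0.30 |
| Nonignorable (n = 92, 1,000 runs) | −0.30 | −0.59 | −0.59 |
| Nonignorable, correlation 0.3 (n = 200,000) | −0.30 | −0.69 | −0.69 |
| Nonignorable, correlation 0.8 (n = 200,000) | −0.30 | −0.47 | −0.47 |

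In the large samples the two methods agree within about 0.002. When dropout depends on the unseen value, FCS reproduces the MAR answer and its bias. With two time points and no extra predictors this agreement is expected by construction; the simulation illustrates the argument and does not predict this trial's result.

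**The case against.** Several stronger readings are tempting, and the document does not support them.

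- **A reader might infer that the sensitivity analysis itself repeats MAR.** It does not. The article gives that name to the nonignorability indices, which do probe departures from MAR. The fault lies in the step that follows.
- **A reader might infer that imputation is the only safeguard.** The attrition comparison and the indices are also planned. They diagnose, however; imputation is the only correction.
- **A reader might conclude that the imputation will certainly be MAR-only.** That is inferred from the absence of any stated departure. FCS can carry a shift or pattern term, and the references cited for the sentence or a fuller plan may describe one.
- **A reader might expect the result to be presented as proof of robustness.** The article does not say how it would be reported, and anyone who reaches this step has already had a warning from the indices.

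Three further objections have weight. A richer imputation model, using the many scales collected, could give a different estimate from the mixed model; it would still assume MAR, though perhaps more plausibly. The size of delta is not known. And the Study Design section already concedes that a single-arm trial cannot test efficacy rigorously.

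It can also be said that an article may leave imputation details to the full plan. That covers a missing shift range. It does not cover a stated reason that is incorrect: the article names the method and credits it with a property that it lacks in standard form.

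**Conclusion.** The point holds for the conditional remedy only. As written, the plan answers a finding of nonignorability with a method that, in standard form, makes the same assumption as the primary analysis, and wrongly describes that method as suited to nonignorable data.

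The exposure is greatest at 3 months, where more than half of the intention-to-treat sample has no outcome. The multipliers of 0.23, 0.37 and 0.52 rest on the article's counts; any translation into SD units rests on an assumed delta. The conclusion also assumes that no nonignorable term is specified elsewhere.

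Severity is moderate. Feasibility and acceptability, the first objective, do not depend on this step, and uncontrolled change from baseline is in any case preliminary evidence. It still merits correction because the effectiveness results are meant to inform a randomized trial.

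**What to change.** In the Missing Data section, delete the claim that FCS as such is applicable to nonignorable data. State instead that the imputation will be delta-adjusted (pattern-mixture) FCS: impute under MAR, shift the imputed values towards no benefit over a prespecified range, and report the shift at which the conclusion changes. Set the direction of the shift scale by scale, since higher scores are favourable on some measures and unfavourable on others, and apply it on the log-odds scale for the binary violence outcomes.

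The range is for the sponsor's statistician to choose and justify; 0 to 0.5 SD for the scales is only an example. Running the shifts whatever the indices show, or adding a scenario in which missing women return to their baseline level, would be reasonable but is a matter of preference.

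The cost is a change of wording and modest programming, with no new data. Data collection is complete, but the article describes the analyses as still to be done, so the range can be fixed before they are run. The downside is that conclusions may look less favourable under the larger shifts.

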#### Statistical Analyses

To test the effects of THRIVE on primary and secondary outcomes, linear mixed effects model for continuous outcomes and generalized linear mixed effects models for binary outcomes will be used, with subject-specific random intercepts to account for the correlations of longitudinal outcomes measured after the intervention (week 2) and at 1-month and 3-month follow-ups. Covariates, such as recruitment sites, any demographic variables correlated with primary outcomes, type of substance use, and intervention format, will be included as fixed effects in all analysis models. The primary knowledge, attitude, and behavior outcomes will be continuous outcomes, and secondary outcomes such as experience of SV or IPV will be binary outcomes. In addition, with this model, we will also identify postbaseline time points where changes in outcomes from baseline are significant.

## Results

Recruitment, enrollment, and data collection from the 3 sites was completed between June 2024 and March 2025. Of the 92 women recruited and enrolled, 71 (77%) completed the intervention and postintervention assessments, 58 (63%) completed the 1-month follow-up assessments, and 44 (48%) completed the 3-month follow-up assessments. Ten completers, 2 noncompleters, and 2 PSS completed exit interviews. Of the 92 enrolled participants, 45 (50%) were from the Prisma Health Addiction Medicine Center, 42 (47%) from Phoenix Center, and 3 (3%) from Magdalene Clinic. Of the 92 participants, 1 (1%) was American Indian or Alaska Native, 4 (4%) were Black, 1 (1%) were Hispanic, 79 (86%) were White, 2 (2%) identified as multiracial, and 3 (3%) identified as “other.” Racial and ethnic distribution is representative of the patient populations at the recruitment sites. The participants’ mean age was 35 (SD 9.87) years. The most commonly reported substances used included tobacco (79/92, 86%), cannabis (58/92, 63%), alcohol (55/92, 61%), amphetamine-type stimulants (58/92, 63%), and opioids (50/92, 54%; Table 3).

**Table 3 table3:** Types of substances used by enrolled participants (N=92).

Substance types	Participants, n (%)
Tobacco	79 (86)
Alcohol	55 (61)
Cannabis	58 (63)
Opioids (heroin, fentanyl, etc)	50 (54)
Amphetamine-type stimulants	58 (63)
Inhalants	19 (24)
Sedatives	47 (51)
Hallucinogens	32 (35)
Cocaine	44 (48)

## Discussion

### Summary

This study evaluated an interpersonal violence prevention program for women with SUDs to fill a vacuum in programs with demonstrated efficacy for this population. This will be the first study to test an evidence-based SV and IPV prevention program for women in substance use treatment. It will address the nexus of 2 significant public health problems: interpersonal violence and SUDs. Although a majority of women in substance use treatment have a history of SV or IPV, a history of interpersonal violence and risk for repeated exposure to interpersonal violence are rarely addressed in substance use treatment settings.

Both a history of violence and substance use place women at risk for cumulative exposure to violence and adverse outcomes, including SUDs, PTSD, depression, and physical health problems. For women in substance use treatment, exposure to SV and IPV can lead to escalation of substance use and inability to achieve recovery [11]. However, women face barriers to care in seeking trauma-focused services, and there is a lack of available evidence-based violence prevention programs within substance use treatment settings. Therefore, there is a significant need for research to develop and test violence prevention services that could mitigate the sequelae of initial and repeated exposure to interpersonal violence among women in substance use treatment.

An additional gap in the literature that will be addressed by the THRIVE program is the lack of integrated prevention programming for SV and IPV, despite their shared risk factors. These forms of violence share risk factors such as exposure to childhood adversity, stereotypical gender role conformity, and substance use [53]. An intervention that is both pragmatic and designed to achieve maximum impact will address multiple forms of interpersonal violence simultaneously. The THRIVE program is one of only a few programs to adopt an integrated approach to these 2 co-occurring forms of violence [53,89].

THRIVE will also be the only known program to address the use of illicit substances as a risk reduction strategy for violence prevention. Prior prevention programs have singularly focused on alcohol use [46]. However, our data from the program development phase suggested the need to address unique concerns around illicit substance use, such as vulnerability during withdrawal, coercion by dealers, and exchange of sex for drugs.

Furthermore, THRIVE will be the first program to engage PSSs as violence prevention educators. Consistent with recommended models of trauma-informed care in substance use treatment settings [90], we will incorporate trained PSSs as educators who can lift stigma, offer empathy and trust, reduce barriers to engagement, and fill gaps in mental health service provision. While PSSs have delivered prevention programming in the mental health sector [91], this will be the first known study to develop and test a PSS-delivered violence prevention program. In addition, training PSSs in health promotion skills related to violence and substance use will provide them with professional skills and confidence to work with their clientele. A PSS violence prevention model also offers scalable and cost-effective solutions for workforce development and the expansion of mental health services.

Finally, THRIVE places unique emphasis on help seeking and overcoming barriers to care as violence prevention strategies. Encouraging help seeking will promote access to resources that could mitigate mental health conditions and reduce adversity related to exposure to interpersonal violence as a means of both health promotion and risk reduction. Our preliminary research indicates that participants view this content as both necessary and missing from existing prevention programs [48]. One benefit of using PSSs as facilitators is that they are trained and capable of both modeling appropriate resource use and providing warm handoffs to other services.

### Conclusions

Upon successful completion of this study, we expect to demonstrate the feasibility, acceptability, and preliminary effectiveness of THRIVE. This program will address gaps in the evidence base by emphasizing the critical intersection of violence and substance use, expanding effective strategies to a population considered high risk, and implementing a novel peer-delivered format to overcome barriers to care. The limitations of this approach include the use of a single-arm trial, underrepresentation of minoritized populations at our recruitment sites, and flexibility in program format that introduces some variability and could limit generalizability. If preliminary feasibility and efficacy are established, we will use the study findings to design future trials that minimize these limitations by using randomized controlled designs, oversampling underrepresented groups, and standardizing the delivery format. Our long-term goal is to develop an accessible, scalable, and efficacious prevention program that reduces the incidence of exposure to SV and IPV, substance use, and violence-related mental health disorders for women in substance use treatment. Ultimately, reducing exposure to SV and IPV is expected to reduce substance use escalation as well as sustain recovery from SUDs over the long term.

## Abbreviations

IPV: intimate partner violence
PC-PTSD-5: Primary Care PTSD Screen for DSM-5
PI: principal investigator
PSS: peer support specialist
PTSD: posttraumatic stress disorder
SAMHSA: Substance Abuse and Mental Health Services Administration
SUD: substance use disorder
SV: sexual violence
THRIVE: The Healthy Relationships and Interpersonal Violence Education
